### Skin fibroblast extraction

Specialized neurologists from the Neurodegenerative Diseases Research Group at VHIR will perform the biopsy for skin fibroblast isolation. This will allow us to investigate patients’ fibroblast’s mitochondrial function, which was being described as impacted in neurodegenerative diseases such as PD, and thus enabling the opportunity to verify the effect of applying a PA program in these patients.

Skin fibroblast biopsies will be collected before and after the intervention in all three groups. The collected cells will then be cultured, expanded, and frozen at VHIR. Subsequently, the cells will be sent to the Center for Neuroscience and Cell Biology at the University of Coimbra, Portugal for further functional and molecular analysis.

### Mitochondrial analysis

The analysis of mitochondrial function and metabolism in skin fibroblasts from patients will encompass various parameters. Metabolic fluxes of the cells will be assessed using the Seahorse XF^e^96 Extracellular Flux Analyzer [23]. Additionally, mitochondrial membrane potential and morphology will be evaluated using TMRM staining, while cellular oxidative stress will be measured using hydroethidine (HEt) and CM-H2DCFDA. Moreover, ATP levels will be determined using a high-throughput luminescent method [37]. The expression of relevant transcripts associated with mitochondrial biogenesis, stress responses, oxidative phosphorylation, and auto(mito)phagy will also be evaluated [23]. This includes enzymes such as superoxide dismutase, catalase [38], glutathione reductase, parkin and PINK1 proteins, the mitochondrial transcription factor A (TFAM), the regulator of mitochondrial biogenesis (such as PGC1-α), and metabolism (such as AMPK-α) [37]. The evaluation of these parameters aims to unravel the molecular mechanism through which PA promotes mitochondrial metabolism remodeling in PD patients. Furthermore, this analysis seeks to identify new intervention targets for PD and demonstrate, for the first time, that the metabolic and mitochondrial beneficial effects of PA in PD patients can be detected through observable biochemical changes in their skin fibroblasts. By uncovering these biochemically-detectable alterations, we can gain valuable insights into the specific mechanisms underlying the metabolic and mitochondrial improvements resulting from PA, providing a foundation for targeted interventions in PD.

### Statistical analysis

Data
analysis
will
be performed using SPSS v.20 (IBM SPSS Statistics). Regarding
descriptive
analysis, all
the variables of
the
sample
will
be analyzed by
means
of
relative
and
absolute frequencies, as
well
as measures of dispersion and
central
tendency frequencies. Repeated measures analysis will be performed using the appropriate mixed effects model, accounting for homogeneous or inhomogeneous samples. This analysis will determine the possible changes between the different moments of the intervention and to evaluate which types of intervention yield the greatest physical benefits, whether in terms of mitochondrial function, physiological factors, quality of life, or cognitive and emotional aspects. Spearman’s
rho
and Pearson’s
r
will
be
used
to
evaluate
the
association
between
two variables that
have
ordinal categories. The
normality
of
the
distribution
of
the results for each
group´s results will
be assessed using the Shapiro-Wilk normality
test, with a significant threshold set at α = 0.05. If
the
data follow a normal
distribution, a parametric paired t-test will be conducted. Otherwise, the Mann-Whitney test
will
be
used. Statistical significant differences will be considered for statistical test
values
with
p<0.05.

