### Sample size calculation

The sample size for this study was determined using the GRANMO program with the model of observed proportions with respect to a reference. For the calculation it has been taken into account that the "maximal respiration” is the key indicator to determine the effects of PA on mitochondrial function, because the entire respiratory chain is forced to the maximum. The calculation has been made accepting an **α** risk of 0.05 and a beta risk of less than 0.2 in a two-sided contrast. Based on preliminary data, there is a difference of "maximal respiration" equal to or greater than 0.263 units [23]. It is assumed that the proportion in the reference group is 0.019 in people older than 50 years [30]. Being an interventional study, the percentage of necessary replacements has been predicted to be 20%.

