### Eligibility criteria

To be included in this study, subjects must meet specific criteria. These criteria include having a medical diagnosis of idiopathic PD, falling within stages of I-III on the H&Y scale in the ‘on’ phase, and demonstrating a good cognitive status with a score 26 or higher on the Montreal Cognitive Assessment (MoCA). Participants must be between 50 and 70 years old and capable of walking independently for at least six minutes. In addition, it is important that the subjects have not made any changes to their medication regimen in the last month. The International Physical Activity Questionnaires (IPAQ) will be used to normalize the groups based on the basal levels of PA [31]. Once the subjects are selected, they will receive a detailed explanation of the research procedures, and the subjects will voluntarily express their consent to participate in this study, signing the informed consent.

Certain criteria will lead to the exclusion of subjects from participation in this study. These criteria encompass the presence of any pathology other than idiopathic PD, cognitive impairment with a MoCA score below 26 points, uncontrolled cardiovascular disease, diabetes, visual impairment, or recent musculoskeletal disorders in the upper or lower extremities that may interfere with balance and locomotion. Additionally, individuals currently undergoing another therapeutic exercise protocol or who have undergone surgery aimed at influencing a specific PD symptom will not be eligible to participate.

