### Randomization

All patients who provide their consent to participate in the study and fulfil the inclusion criteria will be randomized. A sample block randomization method will be employed, dividing the participants in three groups: two intervention groups and one control group. The allocation of individuals to intervention or control groups will be blind to assessors and participants. An independent investigator, uninvolved in the study, will perform the random assignment of subjects into the three groups. This will be done using a computer-generated random allocation table, stratified based on the PD stages (i.e., according to H&Y classification stages I, II, III), basal physical activity levels, sex, and age.

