### Baseline assessment

Each participant will need to sign an informed consent prior to being interviewed. The interview will include a comprehensive medical history review and a complete anamnesis including the collection of medication control, gathering data on their current health status and also the chronology of their specific pathology. The clinical history and neurological examination will be prepared to confirm inclusion-exclusion criteria, assessing motor strength, muscular tone and pathological reflexes. Familiarization sessions will also be conducted before the intervention. In this session, the participants will be provided with a smart band (Amazfit Band®) in order to normalize the basal levels of PA that the patients may have throughout the study.

Both intervention and control groups will undergo a baseline evaluation, including
functional
assessment, PA
tests, motor
assessment, medication control, health
assessment and skin biopsy (small tissue samples) for fibroblast extraction from the skin of the neck.

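### The named analyses do not condition the between-arm comparison on baseline maximal respiration; ANCOVA or a constrained-baseline mixed model would, for one degree of freedom

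*Protocol article*

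**What the plan says.** All references are to the protocol article.

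- **Statistical analysis.** The main method is given as: "Repeated measures analysis will be performed using the appropriate mixed effects model, accounting for homogeneous or inhomogeneous samples". Its stated purpose is to find changes between the moments of the intervention and to see which programme does best. The section then names a paired t-test if a Shapiro-Wilk test does not reject normality, and a Mann-Whitney test otherwise. It lists no model terms.
- **Skin fibroblast extraction.** Biopsies are taken before and after the intervention in all three groups, so the primary outcome has one pre and one post value. **Baseline evaluation** puts the clinical tests at baseline, 3 months and 6 months.
- **Randomization.** Allocation is stratified on H&Y stage (I, II, III) and on "basal physical activity levels, sex, and age".
- **Eligibility criteria.** The IPAQ "will be used to normalize the groups based on the basal levels of PA".
- **Baseline assessment.** A smart band is handed out "in order to normalize the basal levels of PA that the patients may have throughout the study".

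**The concern.** The trial has 8 patients per arm, so chance imbalance in baseline maximal respiration can be sizeable and precision is scarce. The baseline biopsy is the obvious covariate and is already being taken from every patient. Yet each method named leads elsewhere:

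- The repeated-measures model, in its usual form with a free mean for each arm at each time, yields a difference in change scores.
- The paired t-test compares moments within one arm and makes no comparison between arms.
- The Mann-Whitney test compares independent groups. On post-intervention values it ignores baseline altogether.

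The last two are also not substitutes for each other, because they answer different questions. At stake is a wider confidence interval than the data require, and between-arm conclusions drawn from within-arm tests.

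A side issue is the smart band. Activity recorded throughout the study is not basal, and two arms are assigned three 60-minute sessions a week. If such data were ever used as a covariate, part of the exercise effect would be removed.

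**Working it through.** **1. The plan's own figure.** The Sample size calculation was made "using the GRANMO program with the model of observed proportions with respect to a reference", with an alpha "risk of 0.05 and a beta risk of less than 0.2 in a two-sided contrast". It assumes that "the proportion in the reference group is 0.019 in people older than 50 years", a difference of 0.263 and 20% replacements. With p0 = 0.019 and p1 = 0.019 + 0.263 = 0.282:

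n = [1.96·√(0.019·0.981) + 0.842·√(0.282·0.718)]² / 0.263² = 6.04

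6.04/0.8 = 7.55, which rounds up to 8 per group and 24 in total. (Rounding up to 7 before inflating gives 9.) The figure reproduces. The formula has no baseline or covariate term, so the stated size does not depend on this point.

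**2. What the named mixed model estimates.** With two time points, complete data and free arm-by-time means, the arm-by-time contrast equals the difference between arms in mean change. Take equal variances before and after (SD = 1) and pre-post correlation ρ:

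- change score: variance per patient 2(1 − ρ)
- ANCOVA: 1 − ρ²
- ratio: (1 − ρ²)/[2(1 − ρ)] = (1 + ρ)/2

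**3. Size at 8 per group.** The minimum detectable difference (MDD) is for one pairwise contrast with error pooled over three arms, two-sided alpha 0.05, 80% power and a noncentral t distribution, without multiplicity adjustment. Change score: 21 df. ANCOVA: 20 df, with variance multiplied by 1 + 1/19 for estimating the slope. The article gives neither ρ nor an SD, so ρ is assumed and MDDs are in outcome SDs.

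| ρ (assumed) | Variance ratio | MDD, change score | MDD, ANCOVA | Reduction |
|---|---|---|---|---|
| 0.3 | 0.65 | 1.74 | 1.44 | 17% |
| 0.5 | 0.75 | 1.47 | 1.31 | 11% |
| 0.7 | 0.85 | 1.14 | 1.08 | 5% |
| 0.8 | 0.90 | 0.93 | 0.91 | 2% |

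A t-type comparison of post values alone has an MDD of 1.47 at every ρ. ANCOVA is therefore better than both simpler analyses at each value examined.

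If 20% are lost and not replaced, 8 × 0.8 = 6.4, or about 6 per group. At ρ = 0.5 the MDD is then 1.73 for change scores and 1.56 for ANCOVA.

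**4. Adding the stratification factors.** Count H&Y stage as 2 df and activity, sex and age as 1 df each, 5 df in all. The residual df falls to 15 and the variance is multiplied by (1 − R²)(1 + 6/14), where R² is the share of residual variance the factors explain. At ρ = 0.5 and 8 per group:

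- baseline only: 1.31
- plus four factors, R² = 0: 1.55
- R² = 0.1: 1.47
- R² = 0.3: 1.30

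Break-even is near R² = 0.3. At 6 per group the MDDs with the factors are 2.08, 1.98 and 1.74, against 1.56 without, so even R² = 0.3 does not break even.

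**5. Adjusting for activity measured after randomisation.** This was simulated with two arms of 8, a true effect of 1.0, an assumed 1 SD shift in activity and 4,000 runs. When 0, 25, 50, 75 or 100% of the effect runs through activity, the adjusted estimate averages 0.99, 0.76, 0.49, 0.26 or 0.00.

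**The case against.** A condensed article need not list covariates, and a separate analysis plan may do so. A reader might infer that the analysis excludes both the baseline value and the stratification factors. The text does not support that. It is silent on model terms, silence is not exclusion, and a repeated-measures model already contains the baseline value as one of its outcomes. A constrained-baseline mixed model would even fit the wording of the section. This stands, and it limits the point to the methods actually named. It does not remove the point: the stated target is change between moments, and no later plan can put a covariate into a paired t-test or a Mann-Whitney test.

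A reader might also infer that leaving out the four stratification factors wastes precision. The arithmetic does not show it. With 24 patients, adjusting for all four is more likely to cost precision unless they are strongly prognostic.

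Finally, a reader might infer that smart-band data will be adjusted for. No section says that band data enter a model. The Eligibility criteria use the same verb for making the groups comparable on basal activity, and monitoring background activity is at least as natural a reading. The unclear wording justifies a safeguard, not a finding of error.

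The gain from baseline adjustment also rests on an assumed correlation and nearly vanishes at ρ = 0.8.

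**Conclusion.** The point holds in a limited form. The methods named do not condition the between-arm comparison on baseline maximal respiration, and a better method is available at almost no cost. The gain is moderate if the pre-post correlation is low (about 17% in detectable difference at 0.3) and small if it is high (about 2% at 0.8). These figures assume equal pre and post variances and complete data, and no correlation or SD in the article can narrow the range. The planned 24 patients are not called into question here. The document shows neither a deliberate exclusion of covariates nor a planned adjustment for on-study activity.

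**What to change.** - **Primary analysis.** Compare post-intervention (3-month) maximal respiration between arms by ANCOVA adjusted for baseline maximal respiration, or by the equivalent constrained-baseline mixed model. Use the constrained-baseline form for the clinical scales at 3 and 6 months.
- **Simple tests.** Remove the paired t-test and Mann-Whitney sentence as a basis for between-arm conclusions. A within-arm paired test may stay as description.
- **Stratification factors.** Prespecify at most one or two. For example, three-level H&Y stage, continuous age and baseline together take 4 df of the 21 residual df at 24 patients, or of 15 at 6 per arm.
- **Activity data.** Say what normalising means in Baseline assessment. Limit any activity covariate to values from before randomisation, and keep on-study band data descriptive (adherence, background activity in the control arm).

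The cost is a change of wording, made before the post-intervention fibroblast results are examined, and 1 df for the baseline covariate. It needs no extra patients, visits or biopsies.

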### Intervention

Two different programs are designed in order to investigate the effect of PA on mitochondrial function in skin fibroblasts of patients with PD.

The first group (n = 8) will undergo basic physical training (BPT) focused on strength and resistance. The second group will engage in BPT combined with functional exercises (BPTFE), which includes cognitive and dual task training. A third group, the sedentary group, will serve as the control. The intervention in the two PA programs will last 3 months.

The interventions will be conducted in group settings, with 8 patients per group, and each session will last for 60 minutes. The frequency of the sessions will be 3 times a week. The intervention programs will be structured into 3 meso-cycles of 4 weeks. During the initial two weeks, the workloads will be maintained to facilitate the adaptation period. For the BPTFE program, in addition to adapting to the load, participants will also need to adapt to complex motor execution tasks. Starting from the third week, the workload will progressively increase.

In both PA programs, exercises will target the large muscle groups, with a component/emphasis on the eccentric phase of concentration. The *kBox4* Platform, a device designed to maximize performance and training outcomes, will be used to enhance the eccentric phase of the exercises. This device, provided by Exxentric AB (Stockholm, Sweden), a company specialized in innovative and evidence-based training equipment and methods, will be loaned for the study. *kBox4* is controlled by a specific program, *Kmeter*, which records and stores all the information (duration, intensity, repetitions, etc.) of each movement. Exxentric *kBox4* will be adapted with special harnesses, insurances on the wall and in front of support bars, according to the needs of the patients. In addition to the major muscle groups, specific attention will be given to the key muscles involved in the gait cycle, such as the tibialis anterior, medial gastrocnemius, rectus femoris, and hamstrings, from a biomechanical perspective. This aspect will be common to both programs, with the only difference being that the BPT program will have a greater workload due to the division of activity time between functional exercises and Dual Task Training in the BPTFE program.

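### The Shapiro-Wilk screen is put on each group's results, but the paired t-test it selects assumes normal within-patient differences, so skew between patients can needlessly move a paired comparison to Mann-Whitney.

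*Protocol article*

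**What the plan says.** Everything relevant to the rule stands in the Statistical analysis section of the protocol article.

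- **What is screened:** the distribution of each "group´s results will" "be assessed using the Shapiro-Wilk normality" procedure. The section does not mention differences, change scores or model residuals.
- **Threshold:** "test, with a significant threshold set at α = 0.05. If" introduces the choice of test.
- **Consequence:** if the data follow a normal "distribution, a parametric paired t-test will be conducted. Otherwise, the Mann-Whitney test" is used.
- **Other analysis:** "Repeated measures analysis will be performed using the appropriate mixed effects model". The section gives this model the job of finding changes over time and judging which programme does more good, mitochondrial function included.

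The data are paired and the arms small. Under Skin fibroblast extraction: "Skin fibroblast biopsies will be collected before and after the intervention in all three groups". Under Intervention: "The first group (n = 8) will undergo basic physical training (BPT) focused on strength and resistance"; the same section sets 8 patients per group.

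**The concern.** A paired t-test works on one number per patient, the post value minus the pre value. It needs those differences to be roughly normal and makes no assumption about how patients' levels are spread within a group. If a few patients have high respiration at both visits, the levels are skewed, but that part of the spread drops out of the difference. A screen on levels can then reject although the paired t-test is valid.

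A false alarm is costly here because the fallback named is a test for independent samples. It discards the pairing, and with 8 patients the pairing carries most of the information. The section also does not say whether one non-normal group moves all groups to Mann-Whitney or only itself. If only itself, the within-arm p-values of the three arms may come from different tests.

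**Working it through.** The protocol gives no figure for how this rule behaves, so there is none to reproduce. The sample size calculation does not bear on the point.

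**Inputs from the protocol:** 8 patients per arm, three arms, pre and post measurement, Shapiro-Wilk at 0.05, paired t-test or Mann-Whitney, two-sided 0.05.

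**Assumptions, not in the protocol:** post = pre + change; change normal with SD 1, so the paired t-test is exactly valid; between-patient SD 2, with levels normal or log-normal (log-SD 0.75); measurement error split evenly over the two visits; the screen fires if either time point rejects; true mean change 1.2 SD.

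**Step 1. How often the screen fires (n = 8).**

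| Screen applied to | Normal levels | Log-normal levels, log-SD 0.75 |
|---|---|---|
| Pre or post values | about 9% | about 30% |
| Within-patient differences | about 5% | about 5% |

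The rate depends on the assumptions. Milder skew (log-SD 0.3-0.5) gives about 15-22%. Putting all the measurement error on the post value gives 37-38% for log-normal (log-SD 0.75) or exponential levels. With error SD 0.3 of the between-patient SD at each visit and log-SD 0.5 to 1.0, the rate is 22-38% if either time point can trigger and 15-29% for one time point alone. On differences it stays near 5% throughout.

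**Step 2. Power at a true change of 1.2 SD.**

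| Procedure | Power |
|---|---|
| Paired t-test always | about 83% |
| Rule as written | 77% (normal levels) to 65% (log-SD 0.75) |
| Same fallback, screen moved to differences | about 79-80% |
| Screen on levels, paired rank fallback | 83% (normal levels) to 81% (log-SD 0.75) |

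The loss under the rule as written is 83 - 77 = 6 to 83 - 65 = 18 points. With a paired rank fallback it is 83 - 83 = 0 to 83 - 81 = 2 points. In the setting with error SD 0.3 and log-SD 0.8, the rule's power is 60%, and Mann-Whitney alone reaches 19%.

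**Step 3. Type I error.** In that last setting with no true change, the paired t-test rejects in 4.5% of runs, Mann-Whitney in 0.1% and the rule in 2.9%. The harm is lost power, not excess false positives.

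**Step 4. Mixed tests across arms, if the rule runs per arm.** With firing probability q in each of three arms, P(not all the same test) = 1 - (1 - q)³ - q³.

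- q = 0.09: 1 - 0.754 - 0.001 = 0.25
- q = 0.30: 1 - 0.343 - 0.027 = 0.63
- q = 0.05 (screen on differences): 1 - 0.857 - 0.000 = 0.14

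Moving the screen to differences therefore reduces the mixing but does not remove it while the rule is applied arm by arm.

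**Step 5. If variation is multiplicative.** With log-normal levels and changes proportional to level (log-SD 0.5-0.75, change 1.2 within-patient log-SDs), Shapiro-Wilk rejects the raw differences in 18-34% of arms. The paired t-test on the raw scale has power of only 55-70%, and switching to a paired rank test on the level screen gives 68-73%. Here skewed levels are a relevant warning, and the better answer is to choose the scale beforehand.

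**The case against.** Four points can fairly be made against this.

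1. **The harm comes from the fallback.** Largely true: with a paired rank fallback the screen on levels costs 0-2 points. But moving the screen alone, with Mann-Whitney kept, also recovers most of the loss, so the trigger is a defect in the rule as it stands.
2. **The additive model is assumed.** True. Nothing in the protocol establishes it, and under multiplicative variation the raw differences are not normal either. A reader might infer that the rule regularly throws away valid t-tests; the protocol does not support that, because it gives no distribution for maximal respiration.
3. **The mixed model already carries the comparison of programmes.** This stands. A reader might infer that the screen picks the test for the primary outcome, or that the programmes cannot be compared because their p-values come from different tests. The text does not support either: it gives that comparison to the mixed model, so the screen governs the paired comparisons beside it. The section does not, however, say how the two rank.
4. **The wording is condensed.** The word for what is screened is loose and may have been meant as changes. But the object, threshold and both branches are written down, and nothing points to differences. Arm-by-arm switching is likewise allowed rather than stated.

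**Conclusion.** The point holds in limited form. As written, the screen examines a quantity whose normality the paired t-test does not require, and skew between patients can move a paired comparison to Mann-Whitney when the t-test is valid. Under additive data with normal changes, 8 per arm and a change of 1.2 SD, the screen fires in about 9-30% of arms instead of 5%, and power drops from about 83% to 65-77%. Those figures depend on the assumed skew, on either time point being able to trigger, and above all on the unpaired fallback. Different tests in different arms is a possibility that the text leaves open, and it comes from running the rule per arm rather than from the wrong quantity being screened. The matter deserves correction because the rule is explicit, the arms are small and the remedy is cheap.

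**What to change.** In the Statistical analysis section, delete the normality-driven switch. State that the mixed effects model already named is the one fixed analysis for each continuous outcome in all arms, on a scale fixed before the data are seen (for maximal respiration, decide raw or log in advance), with residuals checked graphically.

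If a normality check is kept, apply it to within-patient differences or model residuals pooled over the arms, let it lead to one test for all arms, and make any fallback a paired one.

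The cost is a few sentences: no added patients, visits or assays. It should be done before outcome data are examined.

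### The plan does not say whether the mixed model or the paired t-test/Mann-Whitney pair decides the primary outcome, and the paired test cannot estimate a difference between arms

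*Protocol article*

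**What the plan says.** The Statistical analysis section of the protocol article names two routes to inference.

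- **Mixed model.** "Repeated measures analysis will be performed using the appropriate mixed effects model". Its purposes are to "determine the possible changes between the different moments of the intervention and to evaluate which types of intervention yield the greatest physical benefits", and mitochondrial function is listed among the benefits to be judged.
- **Two-step test.** Each group's results go through a Shapiro-Wilk test. If they look normal, "a parametric paired t-test will be conducted"; if not: "Otherwise, the Mann-Whitney test". Significance is p<0.05.

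The section does not rank the two routes. Elsewhere, the abstract gives three randomised groups of 8, and Skin fibroblast extraction says: "Skin fibroblast biopsies will be collected before and after the intervention in all three groups". The primary outcome, which the sample size section and Table 2 focus on maximal respiration, therefore has one value before and one after the intervention in every arm.

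**The concern.** Randomisation supports three comparisons: BPT minus Sed, BPTFE minus Sed and BPTFE minus BPT. In a parallel design the natural pairing is within a patient, pre against post, so a paired t-test estimates none of the three. Finding significance in an exercise arm but not in control is not a test of the difference between them.

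The fallback makes this worse. The nonparametric counterpart of a paired t-test is the Wilcoxon signed-rank test. Mann-Whitney is for independent samples, so the hypothesis moves from change within an arm to a difference between groups, depending on a normality test with about 8 values.

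A shift common to all arms is what the control arm exists to remove. It could come from culture and expansion of cells from biopsies taken before and after a three-month programme, or from practice on the repeated clinical tests. A within-arm test credits that shift to exercise. The comparison of programmes also has a practical use: the Control group section gives controls, after the final evaluation, the programme with the better results.

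**Working it through.** **1. The plan's own figure.** The Sample size calculation section uses the "model of observed proportions with respect to a reference" with an alpha "risk of 0.05 and a beta risk of less than 0.2 in a two-sided contrast". Inputs: reference p0 = 0.019, difference d = 0.263 (so p1 = 0.282), replacement 20%.

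n = [1.96·√(p0·q0) + 0.8416·√(p1·q1)]² / d²
= [1.96·√(0.019·0.981) + 0.8416·√(0.282·0.718)]² / 0.263²
= (0.2676 + 0.3787)² / 0.0692 = 6.04

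6.04/0.80 = 7.55, so 8 per arm and 24 in all. (Rounding up to 7 before inflating gives 9.) The stated size thus follows from a one-sample comparison with a fixed value; it does not draw on the control arm.

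**2. Which test addresses which question.**

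| Stated analysis | What it compares |
|---|---|
| Mixed model | Time points and intervention types; decisive contrast not named |
| Paired t-test | Pre against post within one arm |
| Mann-Whitney | Two independent groups |

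**3. Error rates if conclusions rest on per-arm paired tests.** The article gives neither the SD of maximal respiration nor the pre-post correlation (rho), so both are assumed: values in SD units, rho 0.5 or 0.7. Setting: 8 per arm, bivariate normal, no arm difference, the same pre-post shift in all arms, 40,000 simulated trials per row, two-sided 5%. The last column is BPT against Sed adjusted for baseline (ANCOVA, residual df 3·8 − 4 = 20).

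| rho | Shift (SD) | One exercise arm significant | At least one of two | At least one, and control not | One named arm, and control not | ANCOVA |
|---|---|---|---|---|---|---|
| 0.5 | 0 | 5.0% | 9.7% | 9.2% | 4.7% | 5.0% |
| 0.5 | 0.25 | 9.7% | 18.2% | 16.5% | 8.8% | 5.0% |
| 0.5 | 0.5 | 23.2% | 40.9% | 31.6% | 17.8% | 4.9% |
| 0.5 | 0.75 | 44.8% | 69.3% | 38.1% | 24.6% | 4.9% |
| 0.7 | 0 | 5.1% | 9.9% | 9.4% | 4.9% | 5.1% |
| 0.7 | 0.25 | 12.6% | 23.4% | 20.6% | 11.1% | 5.2% |
| 0.7 | 0.5 | 35.0% | 58.0% | 37.8% | 22.8% | 5.1% |
| 0.7 | 0.75 | 65.7% | 88.1% | 30.7% | 22.8% | 5.1% |

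Hand check, arms being independent with per-arm rate s: the fifth column is [1 − (1 − s)²]·(1 − s).
- No shift, s = 0.05: 0.0975·0.95 = 0.093.
- rho 0.5, shift 0.5, s = 0.232: 0.410·0.768 = 0.315.
- rho 0.7, shift 0.5, s = 0.350: 0.5775·0.65 = 0.375.

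The ANCOVA column is a single contrast, so its like-for-like partner is the named-arm column. With no shift the two agree; the 9% there only reflects two exercise arms each tested at 5%. The excess from the paired test appears once there is a common shift.

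**4. What the between-arm contrast can detect.** From the noncentral t with 20 df, the difference detectable with 80% power at 8 per arm is 1.47 SD (rho 0), 1.28 SD (rho 0.5), 1.05 SD (rho 0.7) or 0.88 SD (rho 0.8).

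**The case against.** The strongest reply is that the paired t-test is not the only stated analysis. The mixed model comes first in the section, and one of its purposes is to "evaluate which types of intervention yield the greatest physical benefits". Biopsies are taken in all three arms and the Discussion announces a comparison of the two programmes. A reader might infer from the paired t-test that the trial never compares exercise with control, or that the control arm plays no part in inference. The text does not support that: it is true of the paired test but not of the plan.

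Three further replies have weight.

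- **Condensed source.** The article condenses a full protocol, so unstated model terms and contrasts are not in themselves a fault. This stands. What remains is in the printed text: a within-arm test at p<0.05, an unpaired fallback, and no order of precedence.
- **Baseline.** One might infer that baseline is wasted. A repeated-measures model already uses it as an observation, so ANCOVA against such a model is a choice between valid analyses. Against simple change scores the variance ratio is (1 + rho)/2, that is 0.75 at rho 0.5 and 0.85 at 0.7: useful, but not the main issue.
- **Size of the shift.** The article does not say whether pre and post cells are assayed together, so a 0.5 SD shift is conjecture. This stands, and is why a range is shown.

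None of these replies makes the paired t-test/Mann-Whitney pair coherent.

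**Conclusion.** The concern holds as one of unresolved precedence and mismatched tests. The plan contains an analysis that could answer the randomised question and another that cannot, and leaves open which one decides maximal respiration. The within-arm test also switches to a different hypothesis when normality is rejected.

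The size depends on assumptions. If conclusions were drawn from per-arm paired tests and no exercise effect existed, the misleading pattern (an exercise arm significant, control not) would occur in about 9% of trials with no common shift, 17% at 0.25 SD and 32% at 0.5 SD with correlation 0.5, and 38% at 0.5 SD with correlation 0.7. A baseline-adjusted between-arm contrast holds at about 5% throughout. If the mixed model with an arm comparison is in fact decisive, these inflated rates do not apply, but the text should say so.

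**What to change.** - **Maximal respiration.** State that the between-arm contrast at 3 months, adjusted for baseline, decides. Either an ANCOVA of the post value on arm and baseline, or the planned mixed model with an arm-by-time contrast and baseline adjustment, will serve. In the mixed model, enter baseline as a covariate or as a response with a common mean across arms, not both.
- **Reporting.** Give BPT minus Sed, BPTFE minus Sed and BPTFE minus BPT, each with a 95% confidence interval.
- **Scales also measured at 6 months.** Use the mixed model with arm, visit, arm-by-visit and the baseline value.
- **Within-arm changes.** Report them descriptively. Remove the paired t-test/Mann-Whitney switch as a basis for conclusions; if a nonparametric paired summary is kept, use Wilcoxon signed-rank.

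The cost is a rewritten paragraph and one degree of freedom for baseline. All the measurements are already planned, and Trial status places analysis after the last follow-up, so the change can be dated before the data are examined. It does not cure the low power: at 8 per arm only differences of about 0.9 to 1.5 SD are detectable with 80% power, so the intervals should carry the interpretation.
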